## Abstract

**Introduction:**

Real-world data on COVID-19 vaccine effectiveness are needed to validate evidence from randomized clinical trials. Accordingly, this study aims to evaluate, in a real-world setting in Brazil, the effectiveness of Pfizer-BioNTech BNT162b2 against symptomatic COVID-19 and COVID-19-related complications across diverse populations.

**Materials and methods:**

A test-negative case-control study with follow-up of cases is currently being conducted in Toledo, a city in southern Brazil, following a mass COVID-19 vaccination campaign with BNT162b2. The study is being conducted among patients aged 12 years or older seeking care in the public health system with acute respiratory symptoms and tested for SARS-CoV-2 on reverse transcription polymerase chain reaction (RT-PCR). Cases are RT-PCR positive and controls RT-PCR negative. Test-positive cases are prospectively followed through structured telephone interviews performed at 15 days post-enrollment, and at 1, 3, 6, 9 and 12 months. Baseline demographic, clinical, and vaccination data are being collected by means of structured interviews and medical registry records reviews at the time of enrollment. All RT-PCR-positive samples are screened for mutations to identify SARS-CoV-2 variants.

**Ethics and dissemination:**

The study protocol has been approved by the research ethics committee of all participant sites. Study findings will be disseminated through peer-reviewed publications and conference presentations.

**Trail registration:**

**Clinicatrials.gov:**
NCT05052307.

## Introduction

COVID-19, caused by SARS-CoV-2 infection, has affected millions of people around the world. In Brazil, the number of cases has surpassed 28 million, with more than 640,000 deaths from COVID-19 by February 2022 [1]. Therefore, mass-vaccination campaigns using approved COVID-19 vaccines have become a health priority [2].

The Pfizer-BioNTech mRNA COVID-19 vaccine BNT162b2 was approved on June 11, 2021 by the Brazilian National Health Surveillance Agency (ANVISA) for persons 12 years of age and older [3]. A randomized, controlled trial involving 43,448 participants aged 16 years or older showed that a two-dose 21-days apart regimen of BNT162b2 demonstrated 95% efficacy (95% confidence interval [CI], 90% to 98%) against laboratory-confirmed SARS-CoV-2 infection [4]. Related adverse events were reported by 21% of participants (mainly pain at the injection site, fatigue and headache), and were mostly mild-to-moderate in severity. A subsequent randomized, controlled trial involving 2,260 adolescents aged 12 to 16 years showed that a two-dose 21-days apart regimen of the BNT162b2 vaccine demonstrated 100% efficacy (95% CI, 75% to 100%) against laboratory-confirmed SARS-CoV-2 infection, with a safety profile characterized mainly by mild-to-moderate injection-site pain, fatigue and headache [5]. However, evidence regarding effectiveness of BNT162b2 in Brazil, especially against new variants of concern such as Omicron (currently the most prevalent lineage) [6] is limited; likewise, the long-term protection conferred by BNT162b2 vaccination and impact on COVID-19 severity and prolonged symptoms are not yet available.

## Objectives

### Primary objective

The primary aim of this study is to assess the effectiveness of BNT162b2 in preventing symptomatic COVID-19 in a real-world setting in Brazil.

### Secondary objectives

The secondary objectives are to assess the impact of BNT162b2 on: (1) symptomatic SARS-CoV-2 infection caused by circulating variants (e.g., Delta, and Omicron); (2) duration of COVID-19 symptoms; (3) hospitalization for COVID-19; (4) need for ICU admission; (5) need for invasive mechanical ventilation; (6) death from COVID-19; (7) health-related quality of life; (8) persistent COVID-19 symptoms; and (9) symptomatic SARS-CoV-2 reinfection.

## Materials and methods

This study protocol was registered at Clinicaltrials.gov before the enrollment of the first participant (NCT05052307).

### Study setting

This study has been conducted in Toledo (24° 42′ 50″ S, 53° 44′ 34″ W), a city in the state of Paraná, southern Brazil. The population of Toledo was estimated at 144,601 people in 2021. As of 05 February 2022, COVID-19 has affected 38,614 people with 478 deaths. The city secretary of health initiated an age-based COVID-19 vaccination campaign on 20 January 2021, starting with adults 16 years of age and older. A mass vaccination campaign using BNT162b2 for all nonimmunized individuals aged ≥ 12 years was initiated on 27 August 2021 using a two-dose schedule administered 21 days apart. A third dose (i.e., booster dose) of BNT162b2 has been recommended for healthy (according to an age-based prioritization strategy) and immunocompromised individuals aged ≥ 12 years since 15 September 2021. Other available COVID-19 vaccines in Toledo include CoronaVac (Sinovac), ChAdOx1 nCoV-19 (AstraZeneca), and Ad26.COV2.S (Janssen); around 50% of the vaccine-eligible individuals immunized against COVID-19 have received BNT162b2.

Toledo was chosen due to the city standard of care, which provides free healthcare access to a wide variety of COVID-19 diagnosis and management services, and due to the feasibility of accessing information on people who were tested for SARS-CoV-2 through the city surveillance system.

### Study design

The present study is a test-negative case-control study with follow-up of cases (Fig 1). In this design, the same clinical case definition is used for both cases (i.e., participants with symptoms consistent with COVID-19) and controls (i.e., participants without the outcome) [11]. Reverse transcription polymerase chain reaction (RT-PCR) test for SARS-CoV-2 is prospectively used to distinguish cases from controls. Vaccination status and potential confounders are retrospectively ascertained among cases and controls through structured interviews and medical records review. Test-positive cases are prospectively followed through structured telephone interviews performed at 15 days, and at 1, 3, 6, 9 and 12 months.

**Fig 1 pone.0276384.g001:**
[figure not shown]
Study design. MV, mechanical ventilation; RT-PCR, reverse transcriptase polymerase chain reaction; SARS-CoV-2, severe acute respiratory syndrome coronavirus 2.

### Participants

The present study population is composed of consecutive individuals aged 12 years or older who seek the public healthcare system of Toledo with symptoms suggestive of COVID-19.

Inclusion criteria are (1) age ≥ 12 years old; (2) to be a resident of Toledo; (3) seeking care in the public healthcare system of Toledo with symptoms suggestive of COVID-19 defined as follows: acute respiratory infection symptoms (nasal congestion, rhinorrhea, anosmia, sore throat, hoarseness, new or increased-from-baseline cough, sputum production, dyspnea, wheezing, myalgia) OR admitting diagnosis suggestive of acute respiratory infection symptoms (pneumonia, upper respiratory infection, bronchitis, influenza, cough, asthma, viral respiratory illness, respiratory distress, respiratory failure), and (4) having a nasopharyngeal (NP) or nasal sample for SARS-CoV-2 diagnosis obtained as standard of care.

Patients with history of remdesivir treatment in the past 30 days, convalescent plasma treatment in the past 90 days, treatment with monoclonal antibodies for COVID-19 in the past 90 days (e.g., sotrovimab, casirivimab-imdevimab, bamlanivimab, etesivumab), and those who refused to provide informed consent are excluded. Participants are allowed to re-screen; however, the follow-up is performed considering only the first enrollment of each individual for the study.

### Exposures

The primary exposure is the receipt of two or more doses of BNT162b2 according to the Brazilian National Immunization Program (BNIP) recommendations (with the receipt of the second dose 7 days or more before the onset of symptoms of COVID-19-like illness).

Secondary exposures are as follows: (1) receipt of one or more doses of BNT162b2 (with the receipt of the first dose 14 days or more before the onset of COVID-19-like symptoms); (2) receipt of one dose of BNT162b2 (with the receipt of dose, 14 days or more before the onset of COVID-19-like symptoms); (3) receipt of two doses of BNT162b2 (with the receipt of the second dose 7 days or more before the onset of COVID-19-like symptoms); (4) receipt of three doses of BNT162b2 (with the receipt of the third dose 7 days or more before the onset of COVID-19-like symptoms); (5) complete vaccination with other available COVID-19 vaccines in Toledo (CoronaVac [Sinovac], ChAdOx1 nCoV-19 [AstraZeneca], and Ad26.COV2.S [Janssen]) according to Brazil National Immunization Program (BNIP) recommendations.

The reference exposure group is composed of participants who had not received a first vaccine dose before the date of sample collection.

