#### Change in exposure definitions

Given the third vaccine dose of BNT162b2 e became part of standard of care in COVID-19 vaccination in Brazil after study approval, the primary exposure definition was changed from receipt of two doses of BNT162b2 (with the receipt of the second dose 7 days or more before the onset of symptoms of COVID-19-like illness) to receipt of two or more doses of BNT162b2 (with the receipt of the second dose 7 days or more before the onset of symptoms of COVID-19-like illness). We also added the receipt of three doses of Pfizer-BioNTech BNT162b2 mRNA vaccine (with the receipt of the third dose 7 days or more before the onset of symptoms of COVID-19-like illness) as a secondary exposure variable. No data was analysed for this protocol amendment.

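### The primary exposure times only the second dose, so onset 0-6 days after a BNT162b2 booster counts as exposed; a named sensitivity analysis would show whether this matters

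*Protocol article*

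**What the plan says.** All references are to the protocol article.

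- **Primary exposure (Exposures).** "The primary exposure is the receipt of two or more doses of BNT162b2", timed by one condition: "with the receipt of the second dose 7 days or more before the onset of symptoms of COVID-19-like illness".
- **Three-dose exposure (Exposures, secondary exposure 4).** It carries its own window: "with the receipt of the third dose 7 days or more before the onset of COVID-19-like symptoms".
- **One-or-more-doses exposure (Exposures, secondary exposure 1).** Only the first dose is timed, at 14 days or more before onset. Second and third doses have no window.
- **Reference group (Exposures).** "participants who had not received a first vaccine dose before the date of sample collection".
- **How the gap arose (Change in exposure definitions).** After the booster became standard of care, "the primary exposure definition was changed from receipt of two doses of BNT162b2" "to receipt of two or more doses of BNT162b2 (with the receipt of the second dose 7 days or more before the onset of symptoms". The same amendment added the three-dose exposure with its 7-day window on dose 3.
- **Who can enter (Participants; Outcomes).** The entry symptoms include "new or increased-from-baseline cough, sputum production, dyspnea, wheezing, myalgia". One listed symptom is enough for the outcome definition, and no exclusion concerns recent vaccination.
- **Overlap in time (Study setting; Study status).** Boosters were recommended from 15 September 2021. The first participant was enrolled on 3 November 2021, and recruitment was expected to finish in July 2022.

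**The concern.** The amendment widened the exposed group to include boosted people but left the window on dose 2. A person with dose 2 months ago and dose 3 yesterday is in the primary exposed group, is not yet in the three-dose group, and has no clear place in the two-dose group. The authors separated days 0-6 after a booster in one secondary exposure but not in the primary one.

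This could matter because of how a test-negative design recruits controls. If a reaction to the booster produces a listed symptom and the person is swabbed, the test is negative and a vaccinated control is added. Unvaccinated people have no equivalent source of controls. Extra vaccinated controls lower the odds ratio and raise VE. The one-or-more-doses exposure has the same gap for the week after dose 2 or dose 3.

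No planned analysis takes these records out of the primary estimate:

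- The covariates in Primary outcome analysis do not include time since the latest dose.
- The third item in Sensitivity analyses for the primary outcome drops controls by days since symptom onset, not days since vaccination. It may catch some of these controls by chance, but it applies to controls only.
- The time-since-dose analysis in Secondary outcome analyses is a separate, exploratory analysis.

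**Working it through.** **Step 1. The plan's own figure, as a yardstick.** Inputs from Sample size: two controls per case, coverage among controls p0 = 0.90, VE 80% (OR = 0.20), precision width 10%. The 95% level is from Overall principles.

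- p1 = OR·p0 / (1 − p0 + OR·p0) = 0.18 / 0.28 = 0.643
- var(ln OR) = 1/(n·p1·(1 − p1)) + 1/(2n·p0·(1 − p0))
- With n = 622: 1/142.8 + 1/112.0 = 0.0159, so SE = 0.126
- 95% CI for OR = 0.20·exp(±1.96 × 0.126) = 0.156 to 0.256, so VE is 74.4% to 84.4%, a total width of 0.09998

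The smallest n with width at most 0.10 is 622, as the article states. The sample size is not affected by this point. It supplies the scale against which to judge a shift: about 10 points of VE.

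**Step 2. Effect of extra vaccinated controls.** Let r be the number of controls who are in the study only because of a booster reaction, divided by the number of genuine vaccinated controls. They multiply the vaccinated control cell by (1 + r) and change no other cell, so

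OR observed = OR true / (1 + r), and VE observed = 1 − (1 − VE true)/(1 + r).

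The documents give no value for r, so a range is assumed. The planned 1,244 controls include 0.90 × 1,244 ≈ 1,120 vaccinated.

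| r (assumed) | Extra controls | True VE 80% reads | True VE 40% reads |
|---|---|---|---|
| 2% | 22 | 80.4% | 41.2% |
| 5% | 56 | 81.0% | 42.9% |
| 10% | 112 | 81.8% | 45.5% |

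For example, at r = 5%, 0.20/1.05 = 0.190 and 0.60/1.05 = 0.571. A shift from 80% to 85% would need 0.20/0.15 − 1 = 33%. VE 40% is not a planning value in the article. It is shown because the article expects effectiveness to differ by variant (Sample size review) and uses the same model for variant-specific analyses (Secondary outcome analyses).

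**Step 3. Is the range of r plausible?** From 3 November 2021 to the end of July 2022 is about 270 days. Suppose every exposed person were boosted once, evenly over that time, which is a generous assumption. A 7-day window then covers 7/270 = 2.6% of exposed person-time. To reach r = 5% or 10%, booster reactions in that week would have to generate about 5/2.6 = 1.9 or 10/2.6 = 3.9 times the ordinary rate of test-negative visits. If only half were boosted, those multiples double. Values at the low end of the range are easier to believe.

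**Step 4. Precision lost by excluding the window.** If a share of vaccinated cases and controls alike is removed, the CI width at VE 80% moves from 0.1000 to 0.1001 (1% removed), 0.1005 (5%), 0.1012 (10%) or 0.1027 (20%).

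**The case against.** **This is a definition, not an error.** Someone with dose 2 at least 7 days before onset has had two or more doses, whatever the date of dose 3. The three-dose exposure asks a different question and so needs its own window. The amendment is disclosed, and the Discussion lists changes to exposure definitions among the limitations. This stands: a reader might infer that recently boosted people are misclassified or that the article contradicts itself, and it supports neither.

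**The mechanism is assumed.** The Introduction names injection-site pain, fatigue and headache as the main reactions to BNT162b2, and none is an entry symptom. The route needs a listed symptom such as myalgia to follow a booster and to lead to a swab, and the article does not say that this happens. This stands, and the point is therefore conditional.

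**The bias need not be upward overall.** A reader might infer that VE is always inflated. That holds only for reaction visits. People infected before the booster takes effect enter as vaccinated cases, which works the other way. This also stands.

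**Other analyses help, and a fuller plan may cover it.** Separate two-dose and three-dose estimates and the time-since-dose analysis would give a reader some view of recent boosting. The one-or-more-doses analysis is declared exploratory. All true, but none of these changes or tests the primary estimate. An analysis plan that is not shown might code these records differently, yet the exposure definition is fixed in the article and the amended text repeats it.

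**Conclusion.** The point holds as a minor, optional improvement. The primary exposure has no window on the booster, so onset 0-6 days after dose 3 counts as exposed, and no listed analysis removes those records from the primary estimate.

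By the reaction-visit route alone, an assumed 2% to 10% excess of vaccinated controls moves VE up by 0.4 to 1.8 points at a true VE of 80%, and by 1.2 to 5.5 points at 40%. At the planned VE this is small beside the 10-point interval. It would matter more where true VE is low. These figures rest on two assumptions that the documents do not support or refute: that listed symptoms after a booster lead to testing, and the size of r. The net direction, with early post-booster infections counted as well, is not established.

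**What to change.** Keep the present rule as primary and add one item to Sensitivity analyses for the primary outcome: repeat the analysis after excluding participants, cases and controls alike, whose most recent BNT162b2 dose was 0-6 days before symptom onset. Do the same for the one-or-more-doses exposure. The alternative is to attach the 7-day window to the latest dose in both exposure definitions.

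The exclusion must not be limited to controls, because that would itself bias the odds ratio.

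The cost is one sentence, one more analysis and a slight loss of precision (width 0.1000 to 0.1005 if 5% of vaccinated records leave). The BNT162b2 exposures already require dose timing. Data collection says that vaccination status is adjudicated against registry records but does not say so for every dose date, so the availability of third-dose dates should be confirmed. The change should be fixed before database lock.

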### Outcomes

The primary outcome is symptomatic COVID-19, defined by the presence of at least one COVID-19-like symptom as listed in Participants section and confirmed by a positive RT-PCR result for SARS-CoV-2 infection from participants’ NP or nasal swabs.

Secondary outcomes are: (1) symptomatic SARS-CoV-2 infection associated with circulating variants (e.g., Delta, and Omicron); (2) duration of COVID-19 symptoms; (3) hospitalization for COVID-19 within 30 days from enrollment among patients with confirmed COVD-19; (4) need for ICU admission within 30 days from enrollment among patients with confirmed COVD-19; (5) need for invasive mechanical ventilation within 30 days from enrollment among patients with confirmed COVD-19; (6) death from COVID-19 within 90 days from enrollment among patients with confirmed COVD-19; (7) health-related quality of life at 90 days from enrollment among patients with confirmed COVD-19, measured by the three-level version of the EuroQol five-dimensional descriptive system (range, -0.17 [worst] to 1.0 [best]; minimal important difference, 0.03) [7, 8]; (8) persistent COVID-19 symptoms at 180 days from enrollment among patients with confirmed COVD-19; (9) symptomatic SARS-CoV-2 reinfection within 365 days from enrollment among patients with confirmed COVD-19, defined as recurrence of COVID-19-like symptoms confirmed by a positive RT-PCR or antigen test for SARS-CoV-2 more than 90 days after primary infection.

Safety data including adverse events and serious adverse events will be assessed upon inclusion of cases and controls and over the 12-month follow-up for cases, under the standard of care procedures for the city of Toledo’s surveillance program per Brazilian regulatory authority’s requirements.

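### The 'one dose of BNT162b2' exposure also takes in people given one BNT162b2 booster after a complete series of another vaccine, and they count under 'other vaccines' too

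*Protocol article*

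**What the plan says.** All references are to the protocol article.

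- **Exposures, secondary exposure 1:** "1) receipt of one or more doses of BNT162b2 (with the receipt of the first dose 14 days or more before the onset" of symptoms.
- **Exposures, secondary exposure 2:** "2) receipt of one dose of BNT162b2 (with the receipt of dose, 14 days or more before the onset of COVID-19-like symptoms".
- **Exposures, secondary exposure 5:** "5) complete vaccination with other available COVID-19 vaccines in Toledo", naming CoronaVac, ChAdOx1 nCoV-19 and Ad26.COV2.S, according to the national programme.
- **Exposures, reference group:** "The reference exposure group is composed of participants who had not received a first vaccine dose before the date of sample collection". Any product counts here.
- **Exposures, primary exposure:** "The primary exposure is the receipt of two or more doses of BNT162b2 according to the Brazilian National Immunization Program (BNIP) recommendations".
- **Study setting:** "A third dose (i.e., booster dose) of BNT162b2 has been recommended for healthy" and immunocompromised people from 15 September 2021, with no condition on the product used for the primary series. It also says that "around 50% of the vaccine-eligible individuals immunized against COVID-19 have received BNT162b2".
- **Change in exposure definitions:** the exposures were amended because third doses became standard of care. The amendment covers two-or-more and three BNT162b2 doses only. No section assigns mixed schedules to a category.

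**The concern.** A reader will take the one-dose estimate as the protection from partial BNT162b2 vaccination. The wording instead counts BNT162b2 doses and disregards what came before. Someone with a complete series of another product and one BNT162b2 booster is well vaccinated, yet is counted with people who had one injection in total. The same person is also counted in exposure 5, so two estimates meant to describe different groups share members.

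The one-dose VE could then look high because boosted people are inside it. The exposure 5 estimate would in turn combine a primary series alone with a series plus a BNT162b2 booster. The published definitions would show a reader neither effect.

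**Working it through.** **1. The plan's own figure.** Sample size gives 622 cases and 1,244 controls for VE 80% (odds ratio 0.20), 90% coverage among controls, two controls per case and a precision width of 10%.

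- Exposure among cases: 0.20 × 0.90 / (0.10 + 0.20 × 0.90) = 0.643.
- Var(ln OR) = [1/(0.643 × 0.357) + 1/(2 × 0.90 × 0.10)] / n.
- Solving 2 × 0.20 × sinh(1.96 × SE) = 0.10 gives n = 621.7, so 622 cases.
- Enrolment: 622 / 0.5 × 1.2 = 1,493, stated as 1,500.

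The figure reproduces. It concerns only two or more BNT162b2 doses against unvaccinated, so this point does not change it.

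**2. Who meets which definition**, with all lags satisfied:

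| Vaccine history before symptoms | Primary | Exp. 1 | Exp. 2 | Exp. 5 |
|---|---|---|---|---|
| One BNT162b2 dose, nothing else | no | yes | yes | no |
| Complete series of another product only | no | no | no | yes |
| Complete series of another product, then one BNT162b2 dose | no | yes | yes | yes |

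The third row is the problem. It enters both secondary contrasts and stays out of the primary one.

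**3. Are such people plausible?** Study setting lists three other products in use and a BNT162b2 third-dose recommendation from 15 September 2021 that is open as to primary product. Study status dates the first enrolment to 3 November 2021 and expects recruitment to end in July 2022, so enrolment falls within the booster period. The number of such people is not given.

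**4. Effect on the one-dose estimate.** With a common unvaccinated reference, the crude pooled odds ratio is the average of the component odds ratios weighted by their shares among controls. Hence VE(group) = s × VE(mixed) + (1 − s) × VE(single), where s is the mixed-schedule share. Assume VE 80% for mixed and 40% for single:

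- s = 0.3: 0.3 × 80 + 0.7 × 40 = 52%.
- s = 0.7: 0.7 × 80 + 0.3 × 40 = 68%.

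If the two VEs are equal, nothing is distorted.

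**5. A second illustration, starting from planning figures.** Assume that 90% coverage applies to all 3,000 controls and that half of the vaccinated were primed with another product.

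- Primed with another product: 3,000 × 0.90 × 0.50 = 1,350.
- If 10% to 50% of them had one BNT162b2 booster: 135 to 675 controls meet exposure 2 by this route.
- If true single-dose recipients are 3% to 10% of controls (90 to 300), s runs from 135/435 = 0.31 to 675/765 = 0.88.
- With assumed VEs of 70% (mixed) and 30% (single), the group reads 42% to 65% instead of 30%.

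The booster uptake, the single-dose share and the VEs are assumptions.

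**The case against.** **Condensed article.** Coding of mixed schedules often sits in a full protocol or analysis plan, which is not shown, and Data collection says that vaccination status is adjudicated against registry records. This stands in part: the full plan may already handle it. But the article prints each exposure with its dose count and lag, and that wording places the person in three groups. Adjudication confirms which doses were given and does not decide the category.

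**Scope.** Overall principles declares the secondary analyses exploratory, and one BNT162b2 booster after another series does not meet the two-dose primary definition. Both are correct, and they limit the weight of the point.

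**How common are mixed schedules?** A reader might infer that early BNT162b2 boosters mostly followed another primary series, because 27 August + 21 days is 17 September 2021, two days after the booster recommendation. The documents do not support this. The August date starts a mass campaign for the non-immunised and is not stated to be the first use of BNT162b2. The Introduction dates approval to 11 June 2021, and a recommendation date is not a date of receipt. The 50% figure also does not say whether BNT162b2 was given as primary series or booster.

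**Reinfection.** A reader might also infer that the reinfection effect ("symptomatic SARS-CoV-2 reinfection within 365 days from enrollment") is diluted toward no effect, since vaccination data are collected at enrolment and Secondary outcome analyses names no updating for later doses. If only the reference group changes status, a true hazard ratio of 0.4 with half of reference time vaccinated reads 0.4 / (0.5 + 0.5 × 0.4) = 0.57. But cases vaccinated at baseline can also receive later doses. If these cut that group's average hazard to 0.70 of its value, the reading is 0.57 × 0.70 = 0.40, and a larger cut reverses the bias. The assessment schedule (Fig 2) is not shown, so later doses may be recorded. The effect of vaccination before the first infection is also a legitimate target. Neither a defect nor a direction of bias is established.

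**Conclusion.** The point holds for secondary exposures 1, 2 and 5. Followed as written, the definitions put mixed schedules into the one-dose group and let one person count in groups meant to be distinct. The size cannot be fixed from the documents. On the assumptions shown, a one-dose VE of 40% reads 52% to 68%, or one of 30% reads 42% to 65%. These ranges show how the distortion works and are not forecasts; they use crude odds ratios and require mixed schedules to protect better than a single dose.

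The point does not extend to the primary contrast, which is little affected, or to the sample size, which reproduces. That mixed schedules were the majority of early boosters remains an inference. For reinfection, exposure appears to be fixed at enrolment, which justifies at most a sensitivity analysis.

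**What to change.** Before database lock:

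1. Define exposures 1 and 2, and for consistency 3 and 4, as BNT162b2 only, with no other COVID-19 vaccine before symptom onset.
2. Define exposure 5 as other product only, with no BNT162b2 dose before symptom onset.
3. Code another primary series plus a BNT162b2 booster as its own category, kept out of 1, 2 and 5, and report its count among cases and controls.
4. For reinfection, if doses after enrolment are recorded, add a sensitivity analysis that accounts for them. Claim no direction of bias in advance. Note that censoring at a later dose may be informative and that time-varying vaccination brings its own confounding.

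The cost is recoding of registry data already used for adjudication. The downside is a smaller one-dose group with a wider interval. Enrolment targets and the primary model stay as they are. If the full analysis plan already separates mixed schedules, only the published definitions need aligning with it.
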